## Abstract

**Background:**

Interventions for adolescents with externalizing behavior problems are generally found to be only moderately effective, and treatment responsiveness is variable. Therefore, this study aims to increase intervention effectiveness by examining effective approaches to train emotion regulation, which is considered to be a crucial mechanism involved in the development of externalizing behavior problems. Specifically, we aim to disentangle a cognitive and behavioral approach to emotion regulation training.

**Methods:**

A randomized controlled parallel-group study with two arms will be used. Participants are adolescents between 12 and 16 years old, with elevated levels of externalizing behavior problems. Participants will be randomly assigned to either the control condition or the intervention condition. Participants in the intervention condition receive both a cognitive and behavioral emotion regulation module, but in different sequences. Primary outcome measures are emotion regulation skills, emotion regulation strategies, and externalizing behavior problems. Questionnaires will be completed at pre-test, in-between modules, and post-test. Moreover, intensive longitudinal data is collected, as adolescents will complete weekly and daily measures.

**Discussion:**

Gaining insight into which approaches to emotion regulation training are more effective, and for whom, is important because it may lead to the adaptation of effective intervention programs for adolescents with externalizing behavior problems. Eventually, this could lead to individually tailored evidence-based interventions.

**Trial registration:**

The trial is registered at the Central Committee on Research Involving Human Subjects (NL61104.041.17, September 20th, 2017) and the Dutch Trial Register (NTR7334, July 10th, 2018).

## Background

If left untreated, externalizing behavior problems are a serious risk factor for the development of adverse outcomes later in life, such as rejection by peers, school failure, crime involvement and psychopathology [1–3]. Costs to society are estimated to be 10 times higher for youth with elevated levels of externalizing behavior problems than for typically developing youth [4]. Over the past years, knowledge regarding the effectiveness of interventions for externalizing behavior problems in adolescence has increased. These interventions are, however, still found to be only moderately effective and treatment responsiveness is variable [5, 6]. Therefore, this study aims to increase intervention effectiveness by examining effective approaches to train a crucial mechanism involved in behavior problems: emotion regulation.

Emotion regulation is a multidimensional construct, that is defined as the extrinsic and intrinsic processes responsible for monitoring, evaluating, and modifying emotional reactions [7]. Emotion regulation skills entail both the overall trait-level difficulties in regulating emotions (emotion regulation difficulties) and the habitual use of specific adaptive or maladaptive emotion regulation strategies (e.g., rumination) [8]. Both aspects of emotion regulation are found to be related to the development of externalizing behavior problems [9]. For example, emotion regulation difficulties predict increases in aggressive behavior during adolescence [10, 11], whereas the use of adaptive emotion regulation strategies (such as problem solving) are related to less psychopathology [12, 13]. The interplay between the use of adaptive (e.g., problem solving) and maladaptive (e.g., rumination) emotion regulation strategies is also important. Specifically, research shows that for adults who report to use high levels of maladaptive strategies, the use of adaptive strategies is negatively related to problem behavior, whereas this association is non-significant for participants who report to use low levels of maladaptive strategies [14]. So, the use of adaptive emotion strategies might have compensational effects. Similar results are found in adolescents. For example, adolescents who report to use a maladaptive emotion regulation profile (high use of maladaptive emotion regulation strategies combined with the low use of adaptive strategies) are specifically at risk for experiencing externalizing behavior problems [15].

Given the association between emotion regulation and externalizing behavior problems, it is not surprising that aspects of emotion regulation training (e.g., anger management, cognitive problem solving) are incorporated in many evidence-based interventions that aim to decrease externalizing behavior problems [16, 17]. For example, of all interventions targeting externalizing behavior problems in adolescence that are described in recent literature, 75% include an emotion regulation component [16]. In addition, research shows that incorporating aspects of emotion training increases treatment effectiveness [18]. A meta-analysis that investigated the effectiveness of Cognitive Behavioral Treatment (CBT) for anger in children and adolescents showed that the broadly defined construct ‘skills training’ (that includes emotion regulation skills training) was significantly more effective than affective education [18]. It is important to note, however, that these meta-analyses look at broadly defined common components, which, in addition to emotion regulation training, also include for example social skills training or exposure. Moreover, the approaches to train emotion regulation differ. Therefore, we do not know whether different approaches to emotion regulation training are equally effective for all adolescents.

An important differentiation among training approaches seems to be a focus on cognitive emotion regulation (e.g., cognitive reappraisal or problem solving) or behavioral emotion regulation (e.g., behavioral distraction or skills training) [19]. Evidence from literature on coping shows that cognitive and behavioral aspects can be disentangled [20] and that behavioral coping training might be more effective for adolescents than cognitive coping training [21]. However, coping refers to processes that are generated in response to stressful events, whereas emotion regulation refers to responses that are specifically aimed at the response to and modulation of emotions [22]. Results from the coping literature might therefore not be generalizable to the construct emotion regulation. Moreover, adolescents with externalizing behavior problems may have characteristics that make them more or less susceptible to specific training approaches. To our knowledge, the differences in effects between cognitive and behavioral emotion regulation training have not yet been investigated for adolescents with externalizing behavior problems.

On the one hand, indirect evidence suggests that behavioral emotion regulation training might be more effective than cognitive emotion regulation training. Sukhodolsky and colleagues [18] argued that CBT components that were “more behavioral” (e.g., skills development) seemed to be more effective than components that were “less behavioral” (e.g., problem solving). This implicates that treatments that teach actual behaviors might be more effective than treatments that attempt to modify internal constructs. This may pertain particularly to adolescents with behavior problems, who may be less susceptible to cognitive approaches than others because they are on average more impulsive, less verbally intelligent, and less self-critical than their peers [23]. On the other hand, there is also evidence that behavioral training is less effective than cognitive training for adolescents with externalizing behavior problems. Specifically, a meta-analysis by Candelaria and colleagues [24] found that anger management interventions for children and adolescents that used role play (a behavioral technique) were relatively ineffective, compared to other methods such as teaching problem solving or emotional awareness. It has been argued that specific behavior training transfers less to other situations than changing fundamental underlying cognitions. Another possibility is that behavioral and cognitive training approaches are only effective when they are combined, because they supplement or reinforce each other. This is in line with the notion that CBT is developed to integrate cognitive and behavioral therapeutic approaches [25]. If both approaches are useful, the sequence in which they are used may also influence effectiveness. It might be that cognitive changes only transfer to changes in behavior when cognitive training is followed by behavioral exercises. Alternatively, it might be that abstract cognitive instructions are only properly understood after behavioral exercises have made participants familiar with emotion regulation.

The current study therefore aims to examine which approach (cognitive or behavioral emotion regulation training) is more effective in improving emotion regulation skills and reducing externalizing behavior. To this end, we designed an experimental emotion regulation training (the Think Cool Act Cool training) consisting of two modules: cognitive training and behavioral training. These modules are presented to participants in different sequences to examine which (combination of) approaches improve emotion regulation skills and decrease externalizing behavior problems. With this experimental design we aim to test the direct effects on emotion regulation and externalizing behavior problems in order to examine relative contributions. The experiment is not intended to have the pervasive long-lasting effects of comprehensive multi-component interventions and does therefore not include follow-up assessments. To examine changes in emotion regulation and externalizing behavior problems, we will use baseline to post-intervention assessments, and intensive longitudinal data. Specifically, participants will report on weekly changes in aggression and emotion regulation. This allows us to examine dynamic within-subject changes in response to specific training experiences. In addition, this study incorporates a daily diary assessment, in order to examine whether emotion regulation training also effects mood variability. This is important, because emotional dynamics such as mood variability are viewed as an aspect of emotion regulation [26] and research shows that higher mood variability is associated with increases in externalizing behavior problems [26, 27].

In addition, this study will look at the effects of emotion regulation training on comorbid internalizing problems. Research shows that externalizing behavior problems frequently co-occur with internalizing problems such as anxiety and depression [28–30]. A factor that might underlie this co-occurrence is emotion regulation. Emotion regulation is proposed to be a transdiagnostic factor, that relates to heterotypic continuity across externalizing and internalizing behavior problems [8]. For example, a longitudinal study showed that for early adolescent boys, the emotion regulation strategy rumination mediated the transition from aggressive behavior to anxiety symptoms [30]. Given the transdiagnostic nature of emotion regulation, it is possible that an emotion regulation training that aims to decrease externalizing behavior problems, also effects comorbid internalizing problems. If this is the case, a transdiagnostic emotion regulation treatment approach might result in greater treatment efficacy for comorbid conditions [31].

In summary, emotion regulation training is a core component for the treatment of externalizing behavior problems in adolescence, but it is unclear whether cognitive and/or behavioral approaches make this component effective. Therefore, we aim to disentangle the effects of cognitive and behavioral emotion regulation training with an intensive longitudinal experiment. Important moderators and mediators will be taken into account to asses why and for whom which approach is effective.

### Hypotheses

We hypothesize that the Think Cool Act Cool emotion regulation training is effective in improving emotion regulation skills and decreasing externalizing behavior problems, compared to care-as-usual. We also hypothesize that the training has a small effect on mood variability and comorbid internalizing problems. In addition, we compare the contrasting hypotheses that the cognitive (Think Cool) module is more effective than the behavioral (Act Cool) module or vice versa and hypothesize that completing both modules is more effective than completing only one module. In addition, we compare the contrasting hypotheses that it is more effective to first receive the cognitive module and secondly the behavioral module (sequence Think Cool + Act Cool) or vice versa (sequence Act Cool + Think Cool). We expect that overall, emotion regulation mediates the effect of the Think Cool Act Cool training on externalizing behavior problems. In particular, we expect that behavioral emotion regulation mediates the effect of the Act Cool module on externalizing behavior problems and that both cognitive emotion regulation and social information processing mediate the effects of the Think Cool module. Regarding moderation effects, we expect that overall, the Think Cool Act Cool training is more effective for adolescents who report higher levels of affective reactivity, and for adolescents whose parents show more acceptance and less rejection [32, 33]. In addition, we expect that the Think Cool module is more effective for adolescents with higher intelligence, whereas the Act Cool module is more effective for adolescents with lower intelligence [23, 34]. Finally, we expect that higher treatment integrity is related to increased effectiveness [35].

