## Method/design

### Study design

This study is a randomized controlled parallel-group experiment with two conditions and two arms in the intervention condition. Participants are randomly assigned to either the control condition or the intervention condition. Participants in the intervention condition receive both the cognitive and behavioral module, but in different sequences. Specifically, participants in the intervention condition follow either first the cognitive and then the behavioral module (first treatment arm) or the reverse sequence (second treatment arm). In order to minimize contamination between the cognitive and behavioral module, individual participants in the intervention condition are not randomly assigned to a training sequence. Participants in the intervention condition from the same location (i.e. school) who start with the training at the same time (i.e. wave) follow the same sequence. In successive waves at the same school, the sequence will be reversed. An overview of the study design is presented in Fig. 1. Ethical approval for this study was granted by an independent medical ethics committee of the University Medical Center Utrecht.

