**Fig. 2 Fig2:**
[figure not shown]
Spirit diagram. *Note. CAU* Care as Usual

If participants meet the inclusion criteria, they are randomly assigned to either the intervention or the control condition. Randomization takes place at the individual level, by means of computer-generated random numbers. Adolescents, their parents and teachers will obviously notice the condition in which they are participating, so allocation will not be blind. Nevertheless, participants will not be aware of the fact that we examine the difference between two training sequences. Subsequently, adolescent download a questionnaire application on their smartphone and start with the weekly and daily questionnaires. First, a 3-week baseline of the weekly measure (see measures section) will be established. Moreover, adolescents fill in the first Daily Diary measure on five consecutive days. In addition, adolescents, their parents and teachers complete the baseline measures at T1, the first of three assessments. The adolescent questionnaires and tasks are administered individually at school by a trained research assistant at each assessment point. Adolescents fill out the questionnaires on a computer. Teachers fill out the questionnaires on paper. Parents are sent links to the questionnaires via email.

Participants in the intervention condition start with either the cognitive module (Think Cool) or the behavioral module (Act Cool). After 5 weeks, in which participants in the intervention condition follow five individual therapy sessions, all participants, parents and teachers complete the T2 measures. Next, there is a 3-week training break, which allows us to measure possible delayed effects. During the training break, all participants continue to fill in the weekly questionnaire and fill in the second Daily Diary measure. Subsequently, participants in the intervention condition follow the second module (Think Cool or Act Cool, depending on the first module), which also consists of five individual sessions. Eventually, the post-test measures are completed by all participants at T3. There also is a 3-week post-measure of the weekly measure, in which participants also complete the third Daily Diary measure.

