## Discussion

The goal of the current randomized controlled parallel-group study is to examine the effects of the Think Cool Act Cool emotion regulation training. Zooming in on the component emotion regulation allows us to make inferences about the efficacy of this specific treatment component. This will supplement the literature, because current knowledge about intervention component efficacy is mainly based on meta-analyses and reviews, and although these studies inform us which components are associated with larger program effectiveness, they do not allow to make causal inferences [65]. Moreover, the present study examines the differential effects of cognitive and behavioral emotion regulation training. As current interventions for adolescents with externalizing behavior problems are generally found to be only moderately effective [5], this knowledge is important, because it can lead to the future adaptation of current intervention programs.

A specific strength of the current study is that it includes the use of intensive longitudinal data, which allows us to examine dynamic within-subject changes. An additional advantage of this assessment method is that the weekly and daily diary questionnaires are less retrospective than regular measures and therefore might be less susceptible to recall bias [66]. Moreover, the current study will use multiple sources of information, as externalizing behavior problems will be reported by adolescents, parents, and teachers.

Despite the strengths and innovative aspects of the current study, there are some issues that the study is not able to take into account. Because the study does not include a condition in which adolescents receive only the behavioral or the cognitive module, we will not be able to examine follow-up effects of the separate training modules. Nevertheless, as the goal of the current study is to examine direct effects, we also do not intend to examine long-lasting effects. Another limitation of the study is the open design, as adolescents and other informants included in the assessments (parents and teachers) are aware of the fact that they are either in the control or intervention condition. Nevertheless, adolescents are not aware that we examine the difference between two training sequences.

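### Both modules versus one can be tested only as the added gain after the second module; that gain needs the control arm and cannot be credited to combining approaches

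*Protocol article*

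**What the plan says.** The Hypotheses section of the Protocol article says that the investigators "hypothesize that completing both modules is more effective than completing only one module". The Study design section says: "Participants in the intervention condition receive both the cognitive and behavioral module, but in different sequences". The training has an introduction session and five sessions per module, 11 in all.

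The Procedure and randomization section gives the order of events: first module, T2, a 3-week break meant to show delayed effects, second module, T3. On allocation to intervention or control it says: "Randomization takes place at the individual level, by means of computer-generated random numbers". After the first module, "all participants, parents and teachers complete the T2 measures". Later, "Eventually, the post-test measures are completed by all participants at T3". The weekly questionnaire continues in both conditions during the break.

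The Sample size section gives one module-level figure. With 80 participants in the two intervention arms and 19 weekly measurements, a within-subjects analysis is said to detect an effect size of 0.09. That figure is given for the difference between modules. The Analyses section names piecewise growth curves and analysis of variance for the module and sequence questions. It does not name both versus one.

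The Discussion concedes that "the study does not include a condition in which adolescents receive only the behavioral or the cognitive module", and concludes only that follow-up effects of the separate modules cannot be examined.

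**The concern.** At every point of the schedule, all intervention participants have had the same number of modules: one at T2, two at T3. The two states in the hypothesis never exist side by side. Moving from one to the other changes several things together: a second module of different content, five more sessions, 8 more weeks (3-week break plus 5-week module), and any effect of the first module that appears late.

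Two consequences follow. First, if the comparison is made within the intervention participants alone, ordinary change over those weeks counts as benefit of the second module. Second, the Background raises, as one of several possibilities, that "behavioral and cognitive training approaches are only effective when they are combined", and the study aim speaks of finding which combination of approaches works. A further gain at T3 could be read as support for that idea, although a second block of any training, or a late effect of the first, would look the same. The Discussion does not warn the reader of this.

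**Working it through.** **Schedule check.** Sessions: 1 + 5 + 5 = 11, as stated. Weekly measurements: 3 + 5 + 3 + 5 + 3 = 19, as stated. T2 to T3: 3 + 5 = 8 weeks.

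**The plan's module-level figure.** For a within-subjects effect with 80 participants, 19 measurements, alpha 0.05 and power 0.95 (noncentral F), the detectable effect size is 0.100 at a correlation of 0.5 and 0.089 at 0.6. The stated 0.09 is consistent with a correlation near 0.6, which the article does not state. The figure is not in dispute. What matters is that the calculation uses no control participants.

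**What each contrast estimates.** Let m be the effect of the second module, c the delayed effect of the first module that appears after T2, and t the change from T2 to T3 common to both arms.

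- Uncontrolled change in the intervention arm: m + c + t
- Intervention change minus control change: (m + c + t) − t = m + c

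Controls remove t and leave c. Any trend or delayed effect enters one for one, so assumed values of 0.05, 0.15 or 0.30 SD bias the affected contrast by 0.05, 0.15 or 0.30 SD.

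**Simulation.** Inputs: 80 per arm (Sample size section), correlation 0.5 between assessments (assumed), common trend of 0.15 SD from T2 to T3 (assumed), 4,000 repetitions.

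| Assumed truth | Uncontrolled mean | Controlled mean | Controlled rejection rate |
|---|---|---|---|
| m = 0, c = 0 | 0.147 | −0.004 | 5.3% |
| m = 0.25, c = 0 | 0.401 | 0.249 | 35% |
| m = 0, c = 0.15 | 0.298 | 0.149 | 15% |

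The controlled contrast keeps its nominal error rate against a time trend. It does not against a delayed effect of the first module.

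**Combination or more training.** Write m = a + s, where a is what five further sessions of either content would add and s is the surplus from adding the other approach. The data give only the sum: a = 0.15, s = 0 and a = 0, s = 0.15 both yield m = 0.15. Separating them would need an arm with ten sessions of one approach, and there is none.

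**Delayed effects.** T2 precedes the break, and no full questionnaire assessment is scheduled at its end. Only the weekly measure and the Daily Diary run during the break. On the T1-T3 instruments, c is therefore part of T3 − T2. The weekly data can show change during the break, but not a first-module effect that continues into the second module.

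**Precision of the controlled contrast.** The SD of a change score is √(2(1 − ρ)), so the standard error is √(2(1 − ρ)) × √(2/80).

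| | ρ = 0.5 | ρ = 0.7 |
|---|---|---|
| SE, controlled | 0.158 | 0.122 |
| SE, within subjects, √(2(1 − ρ)/80) | 0.112 | 0.087 |
| Power for 0.15 SD | 16% | 23% |
| Power for 0.25 SD | 35% | 53% |
| Power for 0.30 SD | 48% | 69% |
| Detectable with 80% power | 0.44 SD | 0.34 SD |

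The correlations are assumptions, and dropout is ignored.

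**The case against.** The strongest reply is that the hypothesis claims only added benefit, not synergy. More sessions is part of what both versus one means. If each block adds 0.15 SD whatever its content, both modules really are 0.15 SD better than one, and the hypothesis is true. This stands: session dose undermines only the reading that combining the approaches helps. That reading comes from the Background, where it is one of several possibilities, and nowhere does the article say that a T2-to-T3 gain will be reported as evidence for it.

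A second reply is that the break was built in for delayed effects, that piecewise growth curves can model phases separately, and that the exact contrast may be left to a full analysis plan. The break does help, for the weekly and daily measures; it adds no assessment on the main questionnaires. An unstated contrast alone would not be a finding, and the article does not say that controls will be ignored. But no analysis plan can supply a missing arm, and the only module-level calculation shown leaves controls out.

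A reader might go further and infer that the hypothesis cannot be tested at all, or is wholly confounded with time. The documents do not support that: controls are individually randomized and complete T2, T3 and the weekly measure. It is true of sequence that "individual participants in the intervention condition are not randomly assigned to a training sequence", but the contrast with controls, pooled over sequences, does not depend on how sequence was assigned.

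It is also tempting to relabel the hypothesis as ten sessions versus five. That would be no more accurate, because sessions 6 to 10 are always the other module.

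**Conclusion.** The point holds in limited form. The added benefit of the second module over the first, relative to care-as-usual, can be estimated from this design. A within-subjects analysis of the 80 intervention participants would carry any common time trend into that estimate in full. The controlled contrast removes the trend but keeps any delayed effect of the first module on the T1-T3 instruments, and no analysis can attribute the gain to combining cognitive with behavioral content.

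The 0.15 SD values are illustrations, not figures from the article; the true bias equals whatever trend or delayed effect occurs. Removal of the trend assumes that it is the same in both arms. The main intervention-versus-control comparison and its sample size are not affected.

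**What to change.** 1. In the Hypotheses section, restate the hypothesis as the added benefit of a second five-session module over the first, relative to care-as-usual.
2. Test it as (T3 − T2 in intervention) minus (T3 − T2 in control).
3. In the piecewise model of the weekly data, include the controls and give the 3-week break its own segment, so that delayed effects of the first module can be seen.
4. Extend the Discussion's limitation: the design cannot attribute a further gain to combining the two approaches, and only partly separates it from delayed effects of the first module.

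The cost is a more modest conclusion and a less precise contrast. Its standard error is √2 times that of the within-subjects change, and power for an increment of 0.25 to 0.30 SD is about 35% to 69% under the assumed correlations. No new data are needed.
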